#### Randomizing and treatment allocation

Allocation to treatment group will be performed using a stratified four-block randomization procedure with treatment unit as the stratification variable. The randomization will be concealed to the clinicians recruiting patients to the study and is carried out by an independent statistician at the Norwegian Institute of Public Health. After screening and randomizing, the study participants will be followed for one year and meet with a trained research assistant at four checkpoints: T1, T2, T3, T4 (see Fig. 1).

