**Methods/design:**

The study is a multicenter, observer-blinded, superiority, two-armed RCT which will include patients from four clinical departments at Vestre Viken Hospital Trust, Norway. We aim to include 100 patients with moderate to strong suicidal problems, as defined by a score of 13 or more on Beck’s Scale for Suicide Ideation - Current. Patients are included regardless of diagnosis. Randomization will be performed using a stratified four-block procedure with treatment unit as the stratification variable. The duration of treatment will vary depending on patients’ needs and clinical assessments. Patients are interviewed by research staff at four checkpoints: baseline, 2 weeks, 6 months, and 12 months. Central outcome measures are the Beck Scale for Suicide Ideation - Current, Outcome Questionnaire – 45, and Suicide Attempt Self-Injury Count.

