## Methods/design

In a pragmatic RCT, CAMS will be compared with TAU in the department of mental health and addiction, Vestre Viken Hospital Trust, Norway. Vestre Viken Hospital Trust consists of several formerly independent hospitals and institutions, covering 26 municipalities with a population base of 470,000 people. The trial will be conducted at four different outpatient and inpatient treatment units situated in four different geographical areas. At Baerum District Psychiatric Center one general inpatient facility and one acute inpatient facility participate in the trial. One acute in-ward facility at a psychiatric hospital in Asker (Blakstad Hospital) also attends the trial. Furthermore, in Drammen District Psychiatric Center one acute ambulatory outpatient unit and one team within the general outpatient clinic participate. Lastly, at Kongsberg District Psychiatric Center two units are involved: one acute inpatient ambulatory team and one team from the general outpatient clinic. Together, the participating inpatient units admitted approximately 850 patients for hospitalization in 2015. The outpatient clinics saw approximately 2000 patients for treatment. Information is not available regarding the proportion of those treatment courses that were associated with suicidality. However, as reported by Ruud in a representative study, up to 70 % of those seeking acute psychiatric health care in Norway suffer from some degree of suicidal-related problems (thoughts, plans, actions) [7]. Similar figures were reported by Mellesdal and colleagues [6].

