### Power calculation

In calculating power, we use one-sided confidence intervals because previous studies have indicated CAMS to be superior to TAU [18, 23–25]. We use the following assumptions: (1) the main outcome variable BSSI-C score after treatment — which is scored on a 0–38 point scale — has a standard deviation of 7 points [27]; (2) there are equal sample sizes in the experimental and control groups; (3) a four-point difference in BSSI-C scores at follow-up will represent a meaningful clinical difference between CAMS and TAU; and (4) the alpha level is 0.05. Based on these assumptions, 82 % power will be achieved by including 80 participants in the trial, who will be randomized to CAMS or TAU. Assuming a 20 % drop-out rate, our desired sample size is 100 participants at inclusion.

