#### Assessments and measurements

The test battery will be administered by four research assistants. Completion of the baseline and the first follow-up interview (T1, T2) will take approximately 50–70 minutes each. Follow-up screenings after 6 and 12 months each will take approximately 25–45 minutes. We will perform a screener crossover at T3 and T4 so that the research assistant who screens for follow-up is blinded for treatment condition. Treatment condition is not concealed or blinded for the patient or the clinician treating the patient.

The research assistants consist of experienced psychiatric research nurses and psychiatric research health workers and the first author (WR). All have been formally trained for conducting the diagnostic interviews, and one research nurse has previous experience with attending and screening in another research project. The diagnostic interview is conducted in the follow-up interview at T2, after inclusion. After conducting the clinical diagnostic interview, the research assistant discusses and clinically validates the diagnostic conclusion with the first author or with the experienced research nurse. Beyond this, a more formal reliability check on diagnosis will not be carried out. Data will be stored in paper form until all follow-up interviews are completed and then entered into digital form for statistical analysis.

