### Setting

The unique setting of the pragmatic trial generally offers important challenges that may affect motivation of attendance for the involved therapists and also cause recruitment difficulties. For the involved therapists, participation in the study will usually represent an assignment “on top” of daily demands and expectations. Furthermore, as the project is spread out across several units within the clinic, with low representation at each site, the project therapists may experience little co-ownership and companionship in the project as a whole. There are few meeting points with other participants and no possibilities for reducing other work assignments. In this, the study mimics the often lonely and independent reality of a therapist within the mental health services. Low representation of CAMS therapists at each site combined with the need to perform the somewhat unpredictable randomization procedure complicates the inclusion process.

These factors as a whole may hamper clinicians’ motivation and ability to participate actively in the range that we expect, as we rely on each therapist’s inner motivation to take part in the project. In order to meet these challenges, we find it important to continuously motivate and support the participating therapists. Further, continuous communication and anchoring of the project at all levels of leadership as well as persistent offering of information about the project and its possibilities are important. On the other hand, as there are no strong secondary gains to achieve by participating in the study, we expect the research data and results to have high ecological validity.

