Recruitment difficulties (and solutions) cannot be explained by historical and strategic conditions of the trial alone. One obstacle is the high work load among clinicians, which limits their ability to actively participate. A second obstacle may be ambivalence and hesitance towards working within a therapeutic manual over a longer period of time. We have received feedback from some clinicians who feel deprived of clinical autonomy when working within the defined CAMS framework. Other therapists have acknowledged that although a patient may satisfy the inclusion criteria, they refrain from recruiting the patient to the project because they consider TAU to be the “best practice or choice” for the eligible patient. Hence, one factor seems to be acceptance of the randomization procedure and of the project aim (to empirically evaluate the effectiveness of TAU versus CAMS), and another is perhaps paternalism, as noted by Howard [51].

As the CAMS approach enforces an endured focus on suicidality over some period of time, the approach might challenge myths about suicidality [1]. One relevant concern may be the belief that suicidal thoughts and behavior worsen if you talk about and focus on them. Another myth that may affect recruitment is the belief that people who are talking about their suicidal thoughts are truly not in danger. Recently, Law and colleagues [52] reported no indication of harmful effects from repeatedly focusing on suicidal risk and assessments, even for at-risk patients with borderline personality disorder.

Working with suicidal patients often evokes difficult feelings and considerations in both therapists and patients. The CAMS approach brings a clear and endured focus towards the core issues of the patients’ suicidal thoughts and feelings up until the problem is resolved. Consequently, a joint awareness is gained towards the subjective suicidal experiences. As these issues are anxiety provoking, both patient and therapist might seek to avoid or minimize the problem. Unconsciously, this focus may be difficult both for the system as a whole and for the clinicians (e.g., there may be concerns about extended stay at the inpatient clinic if one focuses on the patient’s problems). These factors combined may be at play as we experience recruitment difficulties.

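### Blocks of four within each unit, with open treatment and discretionary invitation, do not secure allocation concealment, and most baseline measures are taken after randomization

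*Protocol article*

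**What the plan says.** **Method of allocation.** The Abstract (Methods/design) says: "Randomization will be performed using a stratified four-block procedure with treatment unit as the stratification variable". The section Randomizing and treatment allocation repeats this: "Allocation to treatment group will be performed using a stratified four-block randomization procedure with treatment unit as the stratification variable". No variation in block size is mentioned. The ratio is not given there, but the Power calculation assumes that "there are equal sample sizes in the experimental and control groups", so 1:1 is the natural reading.

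**Safeguard.** "The randomization will be concealed to the clinicians recruiting patients to the study", and an independent statistician at an outside institute carries it out. The promise names recruiting clinicians and does not mention the research assistants.

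**Openness.** Under Assessments and measurements: "Treatment condition is not concealed or blinded for the patient or the clinician treating the patient". Research assistants are blinded at T3 and T4 only, by swapping screeners.

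**Discretion over entry.** In Recruitment (Methods), the clinician who first assesses the patient gives the information and the invitation, and research assistants help to identify candidates. Under CAMS intervention, recruitment from acute wards aims at patients expected to stay long enough for at least three sessions. Recruitment (Discussion) reports therapists who say that, although a patient qualifies, "they refrain from recruiting the patient to the project because they consider TAU to be the" preferable option for that patient. Setting remarks that, with few CAMS therapists per site, the "somewhat unpredictable randomization procedure complicates the inclusion process".

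**Order of baseline steps.** In Recruitment (Methods), consent comes first, then the BSSI-C and the threshold decision, then randomization. Only after that are the other baseline measures in Table 1 collected. These include SASIC and OQ-45, both listed as secondary outcomes.

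**The concern.** An independent statistician hides the list, but cannot stop staff from deducing the next allocation from earlier ones that are openly known. With a constant block of four, the last place in every block is fixed by the first three. When the first two go to the same arm, the third is fixed as well. In each unit it is visible who treats whom, there are few CAMS therapists per site, and trial staff can be expected to know the block size.

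A predictable next allocation does harm only if someone can act on it. Here invitation is a matter of judgement, and some recruiters prefer one arm. If the patients put forward differ according to the expected arm, the groups differ at entry. Adjustment can deal with that only for characteristics that were measured.

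The order of the baseline steps is a second and separate weakness. OQ-45 and SASIC baselines taken once the arm may be known can be influenced by that knowledge, which makes them less secure as baseline values for those outcomes.

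**Working it through.** **The plan's own figures.** The article gives no figure for predictability. Its sample size is not affected and reproduces: with 40 per arm, a 4-point difference, SD 7 and one-sided alpha 0.05, z = 4/(7 × √(2/40)) − 1.645 = 2.556 − 1.645 = 0.911, so power is 0.819, against the stated 82%. Then 80/(1 − 0.20) = 100.

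**Inputs.**
- Block of four: Abstract, and Randomizing and treatment allocation.
- 1:1 ratio: inferred from the Power calculation.
- Number of strata: Methods/design says "The trial will be conducted at four different outpatient and inpatient treatment units situated in four different geographical areas" but then lists about seven units or teams inside them. Both 4 and 7 are used, which gives about 100/4 = 25 or 100/7 ≈ 14 patients per stratum.
- Total: 100 patients.

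**Certain allocations in a complete block.** There are six equally likely sequences. Two (AABB, BBAA) fix places 3 and 4. The other four fix place 4 only.

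(2 × 2 + 4 × 1)/6 = 1.33 per block, and 1.33/4 = 33.3%.

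**Best guess in a complete block.** The guess names the arm with more places left. The chance of being right is 1/2, 2/3, 2/3 and 1 at places 1 to 4.

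(0.500 + 0.667 + 0.667 + 1.000)/4 = 70.8%, against 50% with no information.

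**Incomplete last blocks.** Spreading 100 patients at random over the strata gives 31.7 certain allocations with 4 strata and 30.4 with 7. The best guess is then right for 70.1% and 69.5%.

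**Varying block sizes.** Simulation with 25 patients per stratum; the observer knows the set of sizes but not their order:

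| Block sizes | Certain | Best guess correct |
|---|---|---|
| 4 only | 32.0% | 70.0% |
| 4 and 6 | 5.8% | 68.3% |
| 4, 6 and 8 | 2.4% | 67.0% |

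**Possible imbalance at entry.** If the patients enrolled differ by δ BSSI-C points according to the guessed arm, and p is the share of correct guesses, the arms differ by (2p − 1) × δ. The article gives no δ. Two points is an assumption, with a range of 1 to 3.

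- Blocks of four, complete: (2 × 0.708 − 1) × δ = 0.417δ, which is 0.83 at δ = 2 (0.42 to 1.25). The value 0.83 is about a fifth of the 4-point target.
- Blocks of 4, 6 and 8, 14 patients per unit, p = 0.668: 0.336δ, which is 0.67 at δ = 2 (0.34 to 1.01).
- Like for like at 25 per unit and δ = 2: 0.80 with 4 only, 0.73 with 4 and 6, and 0.68 with 4, 6 and 8.

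Varying the blocks therefore removes nearly all certainty, but only about a fifth of the bias that an optimal guesser could cause.

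**The case against.** The case on the other side has several parts.

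- **Tracking is needed.** Deduction requires one person who knows the block size and every earlier allocation in that unit, in order. Invitations come from whichever clinician does the first assessment, across scattered sites. This stands: 33% and 71% are upper limits, not descriptions of what staff knew.
- **The preference for TAU is not a response to predicted allocation.** A reader might infer from Recruitment (Discussion) that allocation was being subverted. The text does not support that. It describes a standing view about particular patients, who then enter neither arm. As described, that limits generalizability. It shows discretion and a possible motive, and nothing more.
- **The authors call the procedure somewhat unpredictable.** That remark in Setting counts, if anything, against staff having anticipated allocations, and cannot be used as evidence of predictability.
- **Baseline BSSI-C is measured before randomization.** This is correct, so knowledge of an actual allocation cannot affect it, and an imbalance on it can be adjusted for. Unmeasured differences cannot.
- **The article is condensed.** An unseen full protocol might vary the block size. The article nevertheless states four-block twice without qualification. If sizes do vary, one sentence settles the matter.
- **The remedy barely moves the bias figure.** This is true for an optimal guesser, as the working shows. The main gain is the loss of certainty.

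What remains is that the safeguard described protects the list and not the sequence, and that it does not mention the research assistants. They help to find candidates and rate the interview that decides entry.

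**Conclusion.** The point holds as a weakness of design. The stated blocks of four within unit, with open treatment and discretionary invitation, leave up to one third of allocations (30–32 of 100 once incomplete blocks are counted) open to certain prediction, and about 71% open to a correct guess. This rests on 1:1 allocation, on four-block meaning a constant block size of four, and on an observer who knows that size and follows the unit's whole history. The imbalance of 0.83 BSSI-C point rests further on an assumed 2-point difference and on optimal guessing throughout.

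A reader might go on to conclude that concealment failed or that the arms are biased. The article does not show either. Concealment is not secured, and selection bias is a risk.

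The order of the baseline steps is a plain feature of the text and needs none of these assumptions: OQ-45 and SASIC, among others, are collected after randomization. The sample size and power are unaffected by either issue.

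**What to change.** 1. For all remaining allocations, have the same independent statistician issue a new list with randomly varying block sizes in each unit (for example 4 and 6, or 4, 6 and 8), with the sizes not disclosed to site or research staff. Extend the concealment statement to the research assistants.
2. Release each allocation only after consent, eligibility and the full T1 battery are recorded. Consent and the BSSI-C already come first, so the change is to move the remaining baseline measures, including OQ-45 and SASIC, ahead of randomization.
3. For patients already enrolled, report baseline balance by position within block.
4. Say openly what the change achieves: certain predictions fall from about 32% to about 2–6%, but the best-guess rate falls only from about 71% to 67–68%.

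The cost is one new list and a longer session before allocation. Sample size does not change. The downside is a slightly larger possible imbalance within small units: part-way through a block the arms can differ by up to half the block size, so by 3 patients with a block of six or 4 with a block of eight, against 2 now.

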**Fig. 1 Fig1:**
[figure not shown]
Flowchart and timetable

#### Assessments and measurements

The test battery will be administered by four research assistants. Completion of the baseline and the first follow-up interview (T1, T2) will take approximately 50–70 minutes each. Follow-up screenings after 6 and 12 months each will take approximately 25–45 minutes. We will perform a screener crossover at T3 and T4 so that the research assistant who screens for follow-up is blinded for treatment condition. Treatment condition is not concealed or blinded for the patient or the clinician treating the patient.

The research assistants consist of experienced psychiatric research nurses and psychiatric research health workers and the first author (WR). All have been formally trained for conducting the diagnostic interviews, and one research nurse has previous experience with attending and screening in another research project. The diagnostic interview is conducted in the follow-up interview at T2, after inclusion. After conducting the clinical diagnostic interview, the research assistant discusses and clinically validates the diagnostic conclusion with the first author or with the experienced research nurse. Beyond this, a more formal reliability check on diagnosis will not be carried out. Data will be stored in paper form until all follow-up interviews are completed and then entered into digital form for statistical analysis.

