#### Exclusion criteria

The exclusion criteria are as follows:Age less than 18 yearsSymptom severity and complexity beneath the threshold that elicits rights to necessary health care within specialized care in NorwayKnown or previously diagnosed intellectual disability or dementiaKnown or previously diagnosed developmental disorder such as autism or Asperger’s syndromeOngoing psychosis in terms of active hallucinations and delusions which hamper the ability to provide informed consentPoor Norwegian acquisition which requires a professional translator during the research interviews or the therapeutic processPrevious exposure to CAMS treatment components

The main principle that we follow is that project participants may be included if the symptoms are above threshold as measured by the BSSI-C. The role of informed consent for participation is detailed in the section “Ethics approval and consent to participate.”

The electronic patient journal contains information regarding previous diagnosis and is accessible to the research team and aids the inclusion/exclusion process. If research assistants or clinicians in companionship suspect that an eligible participant has a developmental disorder or intellectual disability, the participant is not recruited into the project for further screening but follows usual treatment procedures in the clinic. If such information or diagnosis is made post hoc after inclusion, the participant will be excluded from further participation. Whether Norwegian language acquisition level is sufficient for inclusion was pragmatically decided to be a clinical judgment, whereby participants with need of a translator during assessment or therapy were excluded. If a patient presents with active psychotic symptoms in terms of hallucinations or delusions, she/he is not invited to participate. If such functioning is identified during the screening process (e.g., by MINI), the patient will be excluded from the trial and will continue with ordinary treatment in the clinic.

Finally, we exclude patients with previous exposure to CAMS treatment components, most notably patients who previously have been administered the SSF. As the entire hospital shares the same electronic patient journal system, we are able to check this before recruiting patients. Use of antidepressants or other kinds of medications is permitted; however, we will register and map their occurrence.

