### Procedures

#### Recruitment

Recruitment is a collaborative process between the research assistants and general clinicians. Clinicians and leaders in the clinics are informed about the project and encouraged to inform and invite eligible patients to participate. Furthermore, four research assistants monitor the patient flow by attending meetings where the general patient flow is handled and processed: morning meetings where newly admitted patients are discussed, intake meetings where referrals for treatment are processed, and other fora where patient referrals are discussed. When potential participants are identified by clinicians or research assistants, the clinician who conducts the first assessment with the patient informs the patient about the project and invites him or her to participate if suicidality is part of the current problem complex. A short invitation letter is compiled for this use. If the patient agrees, he or she will meet with a research assistant to receive detailed information about the project. If the clinician finds that the patient no longer struggles with suicidal-related problems, e.g., the referral letter was misleading, the patient is not invited to participate. Furthermore, if the clinician in the first assessment finds that the patient’s language acquisition requires the use of a translator, she/he will not invite the patient to participate. A close collaboration between the clinic and the research team is essential.

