Interested patients will meet a project assistant who provides thorough and written information about the aim of the study, the study design, and procedures. Ethics, data collection and storage of information, confidentiality, and the possibility to withdraw from the project at any time are also covered in these meetings. All screening interviews with research assistants will be conducted at the clinical unit already familiar to the patient. If an informed consent is offered by the patient, the research assistant follows up with the inclusion screening interview BSSI-C. Eligible participants who are actively suicidal as indicated by a positive score on item SS104 or SS105 and who score 13 or more are accepted for inclusion. At this point the patient is informed whether he or she may be included, and the randomization procedure is performed. Following this, the remaining baseline measures are acquired (see Table 1). Those with scores below the BSSI threshold are excluded from the trial but will receive usual care within the clinic.

**Table 1 Tab1:** Measurements at follow-up

Measures	T1 baseline	T2: 3 weeks	T3: 6 months	T4: 12 months	Outcome (1–10 years)
Primary outcome measure					
Beck Scale for Suicide Ideation - Current (BSSI-C)	x		x	x	
Secondary outcome measures					
Suicide Attempt Self-Injury Count (SASIC)	x		x	x	
Outcome Questionnaire-45 (OQ-45)	x		x	x	
Norwegian Patient Registry data (specified below)					x
Potential moderators and descriptive measures					
MINI		x			
Structured Clinical Interview for ICD-10		x			
Treatment history interview - short form	x		x	x	
Generalized Self-Efficacy Scale (GSE)	x		x	x	
Working Alliance Inventory - Short Revised (WAI-SR Client)		x			
Alcohol/Drug Use Disorders Identification Tests (AUDIT and DUDIT)	x				

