To be approved as a project therapist in the CAMS group, the therapists must conduct three videotaped training therapy sessions following the introductory training. All training therapies were rated by project staff according to the CAMS Rating Scale (CRS), which contains 14 statements covering three main areas of competency: “therapeutic philosophy,” “session framework,” and “overall rating.” Each statement is scored on a 7-point Likert scale. In order to qualify, a mean score of 3 or “satisfactory” (3 or more) was required on the CRS. Of 30 potentially eligible therapists who completed CAMS training, 14 therapists completed the adherence training. Those who completed adherence training met the requirements on the CRS to be approved as a CAMS therapist. Nonetheless, currently only 9 are actively involved and treat recruited patients in the study. After adherence approval, the CAMS therapists are offered supervision from the first author (WR) upon request.

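### Observer blinding of the interviewer-rated primary outcome is not secured: swapping interviewers at T3/T4 leaves open three routes by which a rater can learn the arm

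*Protocol article*

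**What the plan says.** The abstract (Methods/design) makes the claim: "The study is a multicenter, observer-blinded, superiority, two-armed RCT".

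The section Assessments and measurements gives the only mechanism: "We will perform a screener crossover at T3 and T4 so that the research assistant who screens for follow-up is blinded for treatment condition". It adds that patients and treating clinicians are not blinded.

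The same section defines who rates: "The test battery will be administered by four research assistants", and "The research assistants consist of experienced psychiatric research nurses and psychiatric research health workers and the first author". No member of this group is excluded from T3 or T4.

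The section Implementing CAMS and adherence training gives the first author a second role: "After adherence approval, the CAMS therapists are offered supervision from the first author", on request.

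The section Removal from the trial, safety monitoring, and acceptability says that a therapist who ends CAMS or TAU because it is judged insufficient or harmful reports this to the research assistants.

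Table 1 lists "Treatment history interview - short form" at T1, T3 and T4. BSSI-C (primary) and SASIC (secondary) are listed at those same visits. No order within the visit is stated.

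**The concern.** BSSI-C is an interview scale of 19 items scored 0 to 2, and SASIC is a brief interview that sorts self-injuries into suicide attempts and non-suicidal acts. Both leave room for the rater's judgement. Patients and clinicians know the arm, so for these two outcomes a blinded interviewer is the remaining protection against rating bias.

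The direction of any bias is also not neutral. The Power calculation section uses one-sided intervals because earlier studies favoured CAMS, and the Ethics section sees no reason to expect CAMS to do worse. If raters know the arm and share that expectation, scores would tend to move towards CAMS, which is the direction a one-sided comparison is set up to detect.

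**Working it through.** The document gives no figure for blinding, so there is none to reproduce. The check is to set the mechanism against each way a T3/T4 rater could learn the arm.

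**What the crossover removes.** Under Recruitment, randomization takes place during the T1 visit, after the BSSI-C screen and before the remaining baseline measures. The T1 interviewer can therefore know the arm. Giving T3 and T4 to another member of the pool deals with that, and with what was learned at T2. It does nothing about knowledge from other sources.

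**Route 1: the supervisor in the pool.** The first author is one of four assessors and offers supervision to approved CAMS therapists. Nine CAMS therapists are active, and under the leakage procedures they may not see TAU patients. Anyone who knows the CAMS therapists and can link a patient to one of them knows the arm. Where a trial case has been brought to supervision, the supervisor has that link. A crossover that passes the case to the first author at T3 or T4 would make the blinding worse.

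**Route 2: termination reports.** These go to the research assistants, the group that rates outcomes. A report on a named patient from a CAMS or TAU therapist reveals the arm to its recipient. It also arises selectively, for patients whose treatment was judged insufficient or harmful. Nothing says that the recipient must differ from the later rater.

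**Route 3: treatment history in the rating visit.** If these questions come before BSSI-C or SASIC, the rater may hear about treatment before scoring. If they come after, T3 is protected, but an assessor who returns for T4 brings that information along. The order is not stated, nor whether T3 and T4 have different assessors.

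| Source of knowledge | Closed by the crossover? |
|---|---|
| Randomization seen at T1, contact at T2 | Yes |
| Supervision of CAMS therapists by a pool member | No |
| Termination reports to research assistants | No |
| Treatment-history interview at T3/T4 | No |

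**Can the existing staff carry a fix?** Removing the first author from T3/T4 leaves 4 − 1 = 3 raters. If one of those three did both T1 and T2, 3 − 1 = 2 remain, enough for one at T3 and another at T4. If two of the three shared T1 and T2, 3 − 2 = 1 remains and must do both follow-ups. Different assessors at T3 and T4 are therefore often possible, but not always.

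**The case against.** The strongest reply is that the crossover has a stated purpose, a blinded follow-up screener, and that read on those terms it would not assign a case to someone who knows the arm. The article also condenses a full protocol that is not shown, and interview order or instructions to patients may stand there. This has weight: it is why the point is that blinding is not secured, and not that it failed. But the article itself describes roles and a visit schedule that work against its claim, so the point does not rest on omitted detail alone.

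Several stronger readings are tempting and do not hold.

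- *The first author rates follow-up outcomes with knowledge of the arm.* The text places this person in the pool but does not say that they rate T3 or T4. Supervision is on request and is not said to cover trial cases.
- *Assessors learn the arm in unit meetings.* The Recruitment section does say that "four research assistants monitor the patient flow by attending meetings where the general patient flow is handled and processed", but the meetings it names concern new admissions and referrals, largely before randomization.
- *Assessors read the arm in the patient record.* The sentence "The electronic patient journal contains information regarding previous diagnosis and is accessible to the research team" concerns eligibility checks and says nothing about preparing for T3 or T4.
- *The treatment-history interview reveals the arm.* Only its name and schedule are given. Both arms include psychotherapy, typically weekly (in TAU, for outpatients), so accounts of sessions or medication need not identify the arm.
- *A quarter of ratings are unblinded, with a bias of so many points.* One assessor in four does not mean a quarter of interviews. The document gives neither the unblinded share nor any rating shift.

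It is also fair that independent, concealed randomization and the registry outcomes do not depend on the assessors. Those protections stand, but they do not cover the rating of BSSI-C or SASIC.

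**Conclusion.** The concern holds in a limited form. The article claims observer blinding and supports it only with a change of interviewer, which leaves three described routes open: the supervisor's place in the assessor pool, termination reports to the assessors, and a treatment-history interview of unstated order in the rating visit. Blinding of the primary outcome is not secured. The document does not show that any rating was made unblinded.

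The size of any bias cannot be derived from the document, and none is put forward here. The conclusion assumes that no further safeguard exists in the full protocol. If one does, stating it would settle the part it covers. The change is still worth making, because the outcome is rated by interview, the trial states a directional expectation, and the remedy is cheap.

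**What to change.** 1. State that the first author, as CAMS supervisor, does no BSSI-C or SASIC ratings at T3 or T4. The other three assessors cover them.
2. At T3 and T4, complete and score BSSI-C and SASIC before the treatment-history interview. Ask patients beforehand not to name their therapist or treatment. Where possible, use a different assessor at T4 than at T3.
3. Send therapists' termination reports to someone other than that patient's T3/T4 rater. The first author could receive them once out of the rating roster. This changes only who receives the report, not the clinical decision.

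Optionally, record the assessor's guess of the arm after BSSI-C and report its agreement with the true allocation.

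The cost is rostering, interview order and, if the option is taken, one extra item on the form. The downside is less scheduling freedom with three raters in place of four. Excluding everyone who attends a unit's meetings is not advised: the reason for it is weak, and it could leave no eligible assessor.

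According to Trial status, recruitment was still open, so follow-up visits lay ahead to which the change could apply. T3/T4 ratings already made should be identified as done under the former arrangement.
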